**7.3　 Concomitant Medications (Therapies) Regulations**

**7.3.1** **Concomitant Restricted Medications (Therapies)**

None in particular

**7.3.2** **Concomitant Prohibited Medications (Therapies)**

None in particular

**7.4** **Instructions for Research Participants**

The principal (sub-investigator) investigator shall provide the following instructions to research participants before the study begins.

1) Advise participants that when visiting other departments or hospitals, they must inform the attending surgeon or pharmacist of their participation in the study and, whenever possible, consult with their attending surgeon beforehand.

If prior consultation is not possible, instruct them to report to their attending surgeon afterward.

2) Advise participants that if they experience any physical discomfort, they should promptly report it to their attending surgeon and consult about the need for medical care.

3) Instruct participants not to disclose information about this clinical research on social media or similar platforms.

**7.5　 Post-Study Measures**

Efforts will be made to ensure research subjects can receive the best possible diagnosis and treatment based on the study results even after their participation ends.

**7.6　 Individual Research Discontinuation Criteria**

The study will be discontinued if any of the following criteria are met.

1) If the protocol treatment (laminoplasty) cannot be performed within 90 days of registration.

2) If the research subject voluntarily requests to withdraw consent.

3) If, after registration, imaging or clinical diagnosis determines that laminoplasty is not indicated.

4) If intraoperative findings indicate laminoplasty is impossible or if cervical fusion is performed instead of laminoplasty.

5) If intraoperative complications (lamina fracture, vertebral body fracture) necessitate fixation during or after surgery

6) If a major deviation from the protocol is identified, such as violation of the Clinical Research Act and its enforcement regulations, selection criteria, or exclusion criteria

7) If compliance with the protocol becomes impossible

8) If the subject becomes pregnant

9) If the entire study is discontinued

10) If the research subject dies

11) Other cases where the principal investigator or attending surgeon determines continuation of the study is difficult

*The protocol treatment discontinuation date is defined as: the date of determination for cases 1-3), 5)-9), and 11); the surgery date for case 4); and the date of death for case 10).

[Rationale]

These criteria were established to ensure ethical research conduct and to safeguard the safety of research subjects.

[Procedure upon Discontinuation]

When discontinuing the study due to meeting discontinuation criteria, the principal investigator and co-investigators shall take appropriate measures for the subject and clearly document the date/timing of discontinuation, reason, and course of events in the medical records.

Furthermore, if consent is withdrawn after the start of the study treatment, efforts shall be made to clarify whether the cause is due to lack of efficacy of the drug, adverse events (or disease, etc.), or incidental events

(such as relocation). If clinically significant abnormalities (including laboratory values) are identified, appropriate tests shall be performed, and follow-up shall continue until values return to medically acceptable ranges or until the attending surgeon determines follow-up is unnecessary. For adverse events (or diseases, etc.) persisting after study discontinuation, follow-up shall continue until the event resolves or the attending surgeon determines follow-up is unnecessary.

Data obtained from research subjects who withdraw their consent to participate in the study shall be handled according to the subject's wishes: either anonymized and used for research analysis up to the point of submitting the withdrawal of consent form, or all information shall be destroyed.

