(15) The incidence of surgical complications, including reoperations, is a commonly used indicator for evaluating the clinical utility of surgical treatment. Therefore, it was set as a secondary endpoint.

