**8.1.2　Secondary endpoint**

(1) Operative time

(2) Estimated blood loss

(3) Proportion achieving the MCID for recovery in cervical JOA score at postoperative 1 and 2 years

(4) Health-related QOL (EQ-5D) at postoperative 1 and 2 years

(5) Severity of neck pain, upper limb pain, and upper limb numbness (VAS) at postoperative 1 and 2 years

(6) NDI at postoperative 1 and 2 years compared to preoperative

(7) Retention rate of expanded lamina at postoperative 1 and 2 years ^3)^

(8) Proportion of hinge fractures at postoperative 1 and 2 years

(9) Percentage of gutter bone union at postoperative 1 and 2 years^4)^

(10) Cervical spine alignment at 1 and 2 years post-surgery (C-SVA, C2-7 angle, C7 slope)

(11) Paraspinal muscle cross-sectional area (C4/5 level) at postoperative 1 and 2 years

(12) Dural sac area (C3/4, C4/5, C5/6, C6/7 levels) at postoperative 1 and 2 years

(13) Grading of the mass posterior to the dural sac at postoperative 1 and 2 years

(14) Incremental Cost-Effectiveness Ratio (ICER)

(15) Surgical Complication Rates

・Intraoperative complication rate (from start of surgery to completion/closure)

・Early postoperative complication rate (from completion/closure to within 30 days postoperatively)

・Late postoperative complication rate (from postoperative day 31 to within 2 years)

・Mortality rate (entire period: includes non-surgery-related deaths)

・Reoperation rate within 2 years

*For evaluating intraoperative/postoperative complications, use the evaluation criteria from the Japanese Society for Spine Surgery and Related Research database (JSSR-DB) (<https://ssl.jssr.gr.jp/db/>).

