**11．Matters Concerning Access to Original Data and Related Materials**

Original documents in this study include medical records, various test data, surgical records, medication records, patient evaluation sheets, etc.

The Principal Investigator and the research institution administrator shall accept monitoring and audits related to this study, as well as investigations by the Ethics Review Committee and regulatory authorities, and shall guarantee direct access to all original documents and other materials related to this study during such events.

For data recorded in case report forms but not documented in medical records, the following items shall use the case report form entries as the source data:

1) Severity, degree, outcome, date of outcome, causal relationship with protocol treatment, etc., of complications/adverse events, and the rationale for determining causality

2) Date of discontinuation, reason for discontinuation, complications/adverse events causing discontinuation, post-discontinuation course, and results of follow-up

3) Comment from the responsible attending surgeon

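### Section 7.6 does not separate stopping protocol treatment from leaving the study, so patients whose laminoplasty was completed can lose their scheduled 1- and 2-year assessments while remaining in the FAS and SAS

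*Protocol*

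**What the plan says.** Section 7.6 opens its list with "The study will be discontinued if any of the following criteria are met". Item 5 is "If intraoperative complications (lamina fracture, vertebral body fracture) necessitate fixation during or after surgery". Items 6 (major deviation), 7 (compliance impossible) and 11 (continuation judged difficult) leave room for judgement. Section 7.1.4 likewise discontinues the study for a patient converted to fusion and refers to 7.6.

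The date rule in 7.6 uses a different concept: "The protocol treatment discontinuation date is defined as: the date of determination for cases 1-3), 5)-9), and 11". It dates the end of treatment, not the end of observation.

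For the period after discontinuation, 7.6 asks for follow-up of clinically significant abnormalities and adds "For adverse events (or diseases, etc.) persisting after study discontinuation, follow-up shall continue until the event resolves", or until the attending surgeon judges it unnecessary. Section 9.4 has a similar rule for all adverse events. Section 11 accepts the case report form as source for "complications/adverse events causing discontinuation, post-discontinuation course, and results of follow-up".

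The endpoints run longer. Section 8.1.2 lists "Reoperation rate within 2 years" and late complications to 2 years. The rationale for endpoint 15 in section 5.1 says "The incidence of surgical complications, including reoperations, is a commonly used indicator for evaluating the clinical utility of surgical treatment". Section 7.2.1 schedules JOA, imaging and the outcome survey at 1 and 2 years, and 7.2.2 puts reoperation within that survey.

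**The concern.** Once laminoplasty has been done there is no treatment left to stop; only observation remains. Discontinuing the study for such a patient therefore acts on outcome collection alone. Item 5 is triggered by a surgical complication, so the patients affected are selected by a poor operative course.

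The objective in section 4 covers safety as well as efficacy. Reoperation and late complications are endpoints, the QALY model in 8.2 must allow for reoperation, and hinge fracture is read on the 1- and 2-year CT. A rule that can end scheduled observation after a lamina fracture works against all of these. Items 6, 7 and 11 add discretion exercised with the arm known, because the trial is not blinded (5.2.1).

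**Working it through.** **Following one patient through the text.** The assigned laminoplasty is completed, an intraoperative lamina fracture is present, and fixation is later judged necessary.

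1. Analysis sets (10.1): the patient was randomized and had laminoplasty, so belongs to the SAS, and to the FAS provided some data exist after randomization.
2. Item 5 applies, because it covers fixation after surgery as well as during it. The date is that of determination, which would normally precede the fixation.
3. What continues: the persisting fracture is followed (7.6, 9.4), and its course can be entered on the case report form (section 11). The fixation can therefore be recorded.
4. What no passage continues: the 1- and 2-year JOA, CT, MRI and outcome survey, and with them later complications or reoperations unrelated to the persisting event.
5. Analysis: missing values are not imputed (10.4), so a patient without a 1-year JOA drops out of the primary ANCOVA (10.5.2). A patient with neither the 1- nor the 2-year JOA also contributes no response to the secondary MMRM.

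**Reproducing the plan's sample size (10.2).** Inputs: SD 40, margin 20, true difference 0, one-sided alpha 0.025, power 0.90.

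- Normal approximation: n per arm = 2 × (1.960 + 1.282)² × 40² / 20² ≈ 84.1, so 85 per arm, 170 in total.
- Noncentral t: power is 0.8999 at 85 per arm and 0.9032 at 86, so 86 per arm, 172 in total, as stated.
- Dropout: 172 / 0.80 = 215, made even at 216, as stated.

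The stated figures hold, and this point reveals no arithmetic error in them.

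**Possible size in the primary contrast.** The protocol gives no rate of fracture needing fixation, so the following are assumptions. A share f of the anchor arm is lost with true 1-year recovery r, all other patients average 50% (the control value in 10.2), and no plate patient is lost. The difference hidden is f × (50 − r). Power with those patients counted is Φ[(20 − f(50 − r)) / (40 × √(2/86)) − 1.96], at 86 per arm with the SD held at 40. With nothing hidden, this formula gives 0.906.

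| f | Hidden difference, r = 25 to r = 0 (points) | Power if counted, r = 25 to r = 0 |
|---|---|---|
| 1% | 0.25 to 0.5 | 0.90 to 0.89 |
| 3% | 0.75 to 1.5 | 0.88 to 0.86 |
| 5% | 1.25 to 2.5 | 0.87 to 0.82 |
| 10% | 2.5 to 5.0 | 0.82 to 0.69 |

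If the losses fall in the plate arm instead, the shift has the same size and the opposite sign.

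**Rare safety endpoints.** With 108 patients per arm, each uncounted event changes an arm's rate by 1/108 = 0.93 percentage points. The comparison of a low rate can therefore change with a few cases.

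**The case against.** The strongest reply is that 7.6 never says observation ends. It is silent on the scheduled visits, and the date it defines concerns treatment. Persisting adverse events are followed under 7.6 and 9.4, section 11 provides for the course after discontinuation, and 9.1 sets evaluation of adverse events and surgical complications to 2 years without a stop at discontinuation. Table A in 8.2 counts some intraoperative injuries at the operation itself.

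This defeats a stronger reading that a reader might infer, namely that every fixation performed after surgery under item 5 is lost from the 2-year reoperation rate. The documents allow it to be recorded; they do not guarantee that it is counted.

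Two further inferences also fail:

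- *That the worst surgical failures in general leave follow-up.* Item 5 names only intraoperative lamina or vertebral body fracture needing fixation. Reclosure, haematoma, infection and implant failure are not listed criteria. Items 7 and 11 could reach them, but nothing shows that they would be used often or differently by arm.
- *That the loss favours non-inferiority.* This depends on the arm affected. Screws are placed in the laminae in the plate arm, and if such fractures were more common there, losing those patients would make non-inferiority harder to show.

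What remains is that provisions for adverse events and source data schedule no JOA, CT, MRI or outcome survey. The wording about discontinuing the study, in both 7.6 and 7.1.4, points towards ending those visits.

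**Conclusion.** The point holds as a conflict of terms with a practical consequence. Sections 7.6 and 7.1.4 treat stopping protocol treatment and leaving the study as one thing, and a centre following the text could end scheduled assessments for patients who remain in the FAS and SAS. The 1-year JOA and later unrelated events would then be missing selectively after a poor operative course, with no imputation.

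The effect on the primary contrast is probably small: about 0.25-2.5 points against the 20-point margin. That range rests on assumed one-arm rates of 1-5% and recovery of 0-25%, neither of which the protocol supplies, and the direction is not established. The consequence is greater for reoperation and late complications, where events are few. Correction is cheap and worthwhile, because outcomes that were not collected cannot be recovered at analysis.

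**What to change.** State in 7.6 and 7.1.4 that, for any patient who underwent laminoplasty, meeting a discontinuation criterion does not end observation unless the criterion is withdrawal of consent, death or termination of the whole study. The scheduled 30-day, 1-year and 2-year assessments then continue: JOA, imaging where clinically permissible, complications, reoperation and survival. The data enter the FAS and SAS analyses. Name the date in 7.6 for what it is, and define a separate date for leaving the study.

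Reconcile 7.6, 7.1.4, 7.2.2, 8.1.2 and section 11 accordingly. The change concerns data collection only; how the surgeon treats the patient stays as it is. Patients who never had laminoplasty are outside both analysis sets and outside this change.

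The cost is a protocol amendment, which needs ethics re-review under 22.2, and a few more case report forms. Section 13.2 describes the visits and tests as comparable to routine care, so the added burden on patients should be small.

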**８．Evaluation Matters**

**8.1** **Evaluation Indicators (Endpoints)**

**8.1.1　 Primary endpoint**

Recovery rate in cervical JOA score before and after surgery

**8.1.2　Secondary endpoint**

(1) Operative time

(2) Estimated blood loss

(3) Proportion achieving the MCID for recovery in cervical JOA score at postoperative 1 and 2 years

(4) Health-related QOL (EQ-5D) at postoperative 1 and 2 years

(5) Severity of neck pain, upper limb pain, and upper limb numbness (VAS) at postoperative 1 and 2 years

(6) NDI at postoperative 1 and 2 years compared to preoperative

(7) Retention rate of expanded lamina at postoperative 1 and 2 years ^3)^

(8) Proportion of hinge fractures at postoperative 1 and 2 years

(9) Percentage of gutter bone union at postoperative 1 and 2 years^4)^

(10) Cervical spine alignment at 1 and 2 years post-surgery (C-SVA, C2-7 angle, C7 slope)

(11) Paraspinal muscle cross-sectional area (C4/5 level) at postoperative 1 and 2 years

(12) Dural sac area (C3/4, C4/5, C5/6, C6/7 levels) at postoperative 1 and 2 years

(13) Grading of the mass posterior to the dural sac at postoperative 1 and 2 years

(14) Incremental Cost-Effectiveness Ratio (ICER)

(15) Surgical Complication Rates

・Intraoperative complication rate (from start of surgery to completion/closure)

・Early postoperative complication rate (from completion/closure to within 30 days postoperatively)

・Late postoperative complication rate (from postoperative day 31 to within 2 years)

・Mortality rate (entire period: includes non-surgery-related deaths)

・Reoperation rate within 2 years

*For evaluating intraoperative/postoperative complications, use the evaluation criteria from the Japanese Society for Spine Surgery and Related Research database (JSSR-DB) (<https://ssl.jssr.gr.jp/db/>).

**8.2** **Evaluation and Recording of Assessment Indicators**

**＜Primary Endpoints＞**

Recovery rate in cervical JOA score before and after surgery

［Definition］

Use the cervical JOA score assessed by the surgeon before surgery and at postoperative 1 or 2 years. The recovery rate calculation formula is as previously reported^4)^, using the following formula:

Cervical JOA Score Recovery Rate = (Postoperative Score - Preoperative Score) / (17 - Preoperative Score) × 100 (%)

The primary analysis time point is postoperative 1 year. Results at postoperative 2 years are also presented as a final analysis.

The same applies to secondary endpoints 3) to 13).

[figure not shown]

Cervical JOA Score (Hirabayashi R et al: Japanese Orthopaedic Association Criteria for Evaluating Treatment Outcomes of Cervical Spinal Cord Disorders. J Orthop Surg Jpn, 68:[contact])

**＜Secondary Endpoints＞**

(1) Operative Time

(2) Estimated Blood loss

[Definition]

Operating time is defined as the time recorded in the anesthesia record.

Blood loss is defined as the amount recorded in the anesthesia log. If “minor bleeding” is recorded, it is considered 10 ml of blood loss.

(3) Proportion achieving the MCID in cervical JOA score recovery rate at postoperative 1 and 2 years

[Definition]

Refer to the description under <Primary Evaluation Items> for the definition of JOA score recovery rate.

Following previous reports19), the MCID for JOA score recovery rate is set at 52.8%. The MCID achievement rate at 1 year and 2 years postoperatively is evaluated for each group.

(4)　 Health-related QOL (EQ-5D) at postoperative 1 and 2 years

[Definition]

Obtained via patient self-completion of the Japanese-language questionnaire (attached separately). If the patient cannot complete the questionnaire due to writing difficulties caused by cervical myelopathy, family members or healthcare professionals will assist with completion.

Health-related QOL will be assessed using the EQ-5D before surgery, postoperative 1 year, and 2 years. Note: The EQ-5D is also used as the utility value when calculating the incremental cost-effectiveness ratio (11).

(5) Severity of neck pain, upper limb pain, and upper limb numbness (VAS) at postoperative 1 and 2 years

[Definition]

Obtained through the patient's own completion of a questionnaire form created in Japanese (attached separately). If the patient cannot complete the questionnaire due to writing difficulties caused by cervical myelopathy, a family member or healthcare professional will assist with completion.

The severity of pain and numbness will be assessed using a 0–100 mm VAS before surgery and at postoperative 1 and 2 years.

(6) Neck disability index (NDI) at postoperative 1 and 2 years compared to preoperative

[Definition]

Data is collected via the Japanese version questionnaire (attached separately) completed by the patient themselves. If the patient cannot complete the questionnaire due to writing difficulties caused by cervical myelopathy, family members or healthcare professionals will assist with completion.

Health-related QOL due to cervical spine disease is assessed before surgery, and postoperative 1 year and 2 years using the NDI total score.

[figure not shown]
(7) Retention rate of enlarged lamina at postoperative 1 and 2 years (Retention rate)

[Definition]

The retention rate is calculated for each enlarged lamina identified on CT scans at postoperative 1 and 2 years, following previous reports^7)^ (Figure 4). The mean retention rate is also calculated for each patient.

(8) Proportion of hinge fractures at postoperative 1 and 2 years

(9) Percentage of bone union of gutter at postoperative 1 and 2 years

[Definition]

Using CT images at 1 and 2 years postoperatively, evaluate the presence or absence of hinge fractures (fractures of the groove created in the medial facet joint) and bone union in each enlarged lamina, following previous reports^8)^. Evaluate both on horizontal slices. A fracture is defined as a complete disruption of the cortical bone continuity of the target lamina. and bone union is defined as the formation of even partial bony continuity within the excavated groove region of the target lamina. The level and lateral side of each lamina are recorded.

[figure not shown]
(10) Sagittal alignment of cervical spine at postoperative 1 and 2 years (C-SVA, C2-7 angle, T1 slope)

[Definition]

Cervical spine alignment (C-SVA, C2-7 angle, C7 slope) is measured from plain radiographs at postoperative 1 and 2 years, according to previous reports^7)^ (Figure 5). Note that the C2-7 angle is denoted with a positive (+) sign for lordosis.

(11) Paraspinal muscle cross-sectional area (C4/5 level) at postoperative 1 and 2 years

[figure not shown]
[Definition]

Measure the cross-sectional area of paraspinal muscles (mm^2^) on the C4/5 slice of T2-weighted images according to a previous report^20)^, and calculate the total values for each side (Figure 6).

(a: multifidus, b: cervical semispinalis, c: cervical splenius capitis, d: splenius capitis)

(12) Dural sac cross-sectional area (C3/4, C4/5, C5/6, C6/7 levels) at postoperative 1 and 2 years

[Definition]

Measure the dural canal cross-sectional area (mm^2^) on the T2-weighted horizontal slice at each of the C3/4, C4/5, C5/6, and C6/7 levels, following the method described in a previous report^21)^ (Figure 7).

(13) Grading of the mass posterior to the dural sac at postoperative 1 and 2 years

［Definition］

The classification of posterior dural canal compression on the central slice of the T2 sagittal image is evaluated according to a previous report^22)^ (Figure 7).

[figure not shown]

(14) Incremental Cost-Effectiveness Ratio (ICER)

[Definition]

Collect direct medical costs at the facility where surgery was performed for each patient at discharge, and at 1 and 2 years post-surgery. Direct medical costs include inpatient treatment costs and outpatient treatment costs for the following services, summing ①, ②, and ③.

① Inpatient treatment costs for DCM surgery (surgery-related costs [surgery, surgical drugs, anesthesia, anesthetic drugs]), excluding surgical fees

② Outpatient costs for DCM after the surgery date (consultations, tests, drugs, other)

③ Rehospitalization costs for adverse events (inpatient treatment fees excluding surgery, surgery-related costs [surgery, surgical drugs, anesthesia, anesthetic drugs])

The cost-effectiveness evaluation metric uses the Incremental Cost-Effectiveness Ratio (ICER). The ICER is calculated by subtracting the control group's costs from the trial treatment group's costs. (ICER). ICER is calculated by dividing the incremental cost—the difference between the trial treatment group's costs and the control group's costs—by the incremental effect—the difference between the trial treatment group's effect and the control group's effect.

The outcome measure used is QALY (quality-adjusted life year). QALY is calculated using a Markov model that accounts for patients requiring reoperation or experiencing death, based on QOL measured by EQ-5D. Utility values and cost values are discounted annually at a rate of 2%, as recommended by the Central Social Insurance Medical Council (https://c2h.niph.go.jp/tools/guideline/guideline_ja.pdf).

(15) Surgical complication incidence

Surgical complications are categorized into intraoperative, early postoperative (within 30 days after surgery completion [wound closure]), and late postoperative (from day 31 after surgery up to 2 years postoperatively) complication rates.

Mortality (all deaths during the study period) and reoperation rate within 2 years postoperatively are recorded independently for complications.

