**7.2****Observation/Examination Items and Schedule**

**7.2.1　Observation/Examination Schedule**

The survey, observation, and evaluation items, along with the visit schedule for this study, are as follows.

|  | Pre-regist.  ~ Regist. | Surg. Date | PO 1 w | Discharge date | PO 30 d | PO 1y | PO 2 y |  |
| --- | --- | --- | --- | --- | --- | --- | --- | --- |
| Allowed Period |  |  |  |  | Within  ±14d | Within  ±56 d | Within ±56d | |
| Registration/Assignment | ● |  |  |  |  |  |  |  |
| Patient Background Information | ●※1 |  |  |  |  |  |  |  |
| Surgery (Protocol Treatment) |  | ● |  |  |  |  |  | |
| Surgery Information |  | ● |  |  |  |  |  |  |
| Intraoperative Complications/Adverse Events |  | ● |  |  |  |  |  |  |
| Early Postoperative Complications/Adverse Events |  |  |  |  |  |  |  |  |
| Medical History/Physical Examination | ●※1 |  | ● | ● | ● | ● | ● |  |
| JOA score | ●※1 |  |  |  |  | ● | ● |  |
| Cervical Plain X-ray  (Cervical Alignment) | ●※1 |  | ● |  |  | ● | ● |  |
| Cervical Plain CT  (Postoperative: Enlarged Laminar Retention Rate, Hinge Fracture/Bone Union) | ●※1 |  | ● |  |  | ● | ● |  |
| Cervical Plain MRI  (Paraspinal Muscle Cross-sectional Area) | ●※1 |  |  |  |  | ● | ● |  |
| Cervical Plain MRI  (Dural sac Area) | ●※1 |  |  |  |  | ● | ● |  |
| Cervical Plain MRI  (Grading of the mass posterior to the dural sac) |  |  |  |  |  | ● | ● |  |
| Late Postoperative Complications/Adverse Events |  |  |  |  |  |  |  |  |
| Health-Related QoL（EQ-5D） | ●※1 |  |  |  |  | ● | ● |  |
| Pain/Numbness Severity (VAS) | ●※1 |  |  |  |  | ● | ● |  |
| Cervical Disability Index (NDI) | ●※1 |  |  |  |  | ● | ● |  |
| Outcome Follow-up |  |  |  |  |  | ● | ● |  |
| Direct Medical Costs |  |  |  |  |  |  |  |  |

● ：Required

※1 : All surveys, observations, and tests related to this clinical study will be conducted after obtaining written consent from the research subjects. However, results from surveys, observations, tests, etc., performed as part of routine care prior to obtaining consent may be used as research data if they were conducted within 360 days prior to registration.

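### With no EQ-5D between surgery and 1 year, the measured utilities behind the ICER miss differences in recovery speed and transient early complications; a form at the existing 30-day visit would partly close the gap

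*Protocol*

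**What the plan says.** Protocol section 8.2(4) sets the timing: "Health-related QOL will be assessed using the EQ-5D before surgery, postoperative 1 year, and 2 years". The schedule in 7.2.1 agrees. The EQ-5D row is marked before registration and at 1 and 2 years, and is blank at 1 week, discharge and 30 days. Those three early contacts already exist in both arms, because history and physical examination are required at each of them.

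The link to the economic endpoint is explicit. Section 8.2(4) adds that "The EQ-5D is also used as the utility value when calculating the incremental cost-effectiveness ratio", and 8.2(14) states that "QALY is calculated using a Markov model that accounts for patients requiring reoperation or experiencing death, based on QOL measured by EQ-5D".

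Costs follow a different calendar. Section 8.2(14) reads "Collect direct medical costs at the facility where surgery was performed for each patient at discharge, and at 1 and 2 years post-surgery", and its third cost item is "Rehospitalization costs for adverse events (inpatient treatment fees excluding surgery, surgery-related costs", continuing with a list of the surgery-related components.

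The rationale for secondary endpoint (14) in section 5.1 makes better cost-effectiveness of the suture anchor part of a key objective of the study.

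**The concern.** A QALY is utility accumulated over time. Section 3.3 argues that the JOA recovery rate changes little after 1 year. If utility behaves similarly, both postoperative EQ-5D values fall on the plateau and none falls in the period of change. Two arms with the same preoperative and 1-year values give the same measured utilities, however differently their patients fared in between.

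Costs and effects are also recorded unevenly. A readmission for an early adverse event at the operating hospital adds to the cost difference. If the patient has recovered by 1 year without reoperation, the measured utilities show no loss. For reoperation the model has a place for the event, but no trial EQ-5D is tied to it, so the utility of that state must be assumed or borrowed from a scheduled 1- or 2-year value.

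This matters because a non-inferiority trial expects nearly equal effects. The denominator of the ICER is then close to zero, and a small omitted QALY difference can move the ratio a long way. An analysis plan can choose model inputs, but it cannot recover trial utilities that were never collected.

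**Working it through.** **The plan's own figures.** The protocol gives no utility, QALY or ICER value, so there is none to reproduce. Its one reproducible design figure is the sample size in section 10.2 (SD 40, margin 20, one-sided 0.025, power 0.9). The t-based calculation gives 86 per arm, 172 in total; 86/0.8 = 107.5, so 108 per arm and 216 in total. Both match the protocol, and neither depends on this point.

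**Inputs.** From the documents: the EQ-5D times (7.2.1, 8.2(4)), the 30-day visit (7.2.1), and material costs of 506,700 and 138,000 yen (3.2). Every utility below is an assumption. Areas are trapezoidal; the protocol states no path.

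**1. Recovery speed.** Assume utility 0.60 before surgery and 0.75 at 1 year, with the plateau reached at month m. The true first-year area is 0.75 − 0.15 × m/24.

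| Plateau reached at | True year-1 QALY | Measured values |
|---|---|---|
| 1 month | 0.744 | 0.60, 0.75 |
| 3 months | 0.731 | 0.60, 0.75 |
| 6 months | 0.713 | 0.60, 0.75 |
| 12 months | 0.675 | 0.60, 0.75 |

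The measurements are identical in all four rows. The largest gap is 0.744 − 0.675 = 0.069 QALY. It affects the ICER only if the arms recover at different speeds.

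**2. Transient complications.** The shift in an arm mean is excess proportion × utility loss × duration in years.
- Low end: 0.05 × 0.1 × 1/12 = 0.0004 QALY.
- High end: 0.10 × 0.3 × 6/12 = 0.015 QALY.

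**3. An assumed arm difference of 0.05 at day 30, with none at baseline or 1 year.** If it is gone by day T, the area is 0.5 × 0.05 × T/365.
- T = 60: 0.5 × 0.05 × 60/365 = 0.004 QALY.
- T = 365: 0.5 × 0.05 = 0.025 QALY.
- From the scheduled EQ-5D values alone: 0.

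**4. What a 30-day value joined by a straight line to 1 year would do.** It always scores 0.025. For T = 60 that is 0.025/0.0041, about 6 times the true area. Its error is 0.025 × (1 − T/365); the error of recording zero is 0.025 × T/365. They are equal at T = 182.5 days, so the straight line is the better choice only if the difference lasts beyond about 6 months.

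**5. Scale on the ICER.** Material gap: 506,700 − 138,000 = 368,700 yen. Assume a measured difference of −0.010 QALY (anchor minus plate).
- As measured: 368,700/0.010 = 36.9 million yen saved per QALY lost.
- With a further −0.004 missed: 368,700/0.0141 = 26.1 million.
- With a further −0.025 missed: 368,700/0.035 = 10.5 million.
- With +0.025 missed instead: −0.010 + 0.025 = +0.015, and the sign of the effect changes.

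This shows sensitivity only. The gap compares three laminae with two and covers materials alone.

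**The case against.** The strongest reply is that the ICER is one of 15 secondary endpoints, that nothing in the protocol contradicts itself here, and that early complications, deaths and reoperations are reported separately. Section 13.2 expects no difference between the arms in complications or safety. The structure of the Markov model may properly be left to the analysis plan. A recovery path common to both arms cancels from the incremental effect. All of this stands, and it limits the point to a cheap improvement in data collection.

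The 0.05 difference is also open to challenge. If each complication cost 0.3 of utility, complications alone would need an excess of 0.05/0.3, about 17 percentage points, to produce it. That stands too: 0.05 is illustrative.

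Stronger readings are tempting, but the documents do not support them:
- A reader might infer that the QALYs cannot reflect any early event. The model is to account for reoperation and death, including early ones, and deficits lasting to 1 year show in the 1-year EQ-5D.
- A reader might infer that early events are costed in full. Costs are collected only at the operating facility, and the adverse-event item covers rehospitalisation.
- A reader might infer that the schedule biases the effect difference towards zero. That needs arms that differ early and then converge, which no passage shows.
- A reader might infer that first-year utility will be interpolated from baseline to 1 year. The protocol does not say so.

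What the reply does not remove is that no measured utility lies between surgery and 1 year. External utilities for health states, if used, would not show whether patients in one arm of this trial recovered faster.

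**Conclusion.** The point holds in a limited form. The EQ-5D is the only utility source named for the ICER, and its timing leaves the first postoperative year unmeasured up to the 1-year visit. Differences in recovery speed, and transient complications without reoperation or death, are invisible to the measured utilities. Reoperation enters the model without a utility measured near the event.

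Neither the size nor the direction is known. Under an assumed 0.05 difference at day 30, the missed amount is about 0.004 to 0.025 QALY, for resolution between day 60 and a linear fade to 1 year. Whether that would alter a conclusion cannot be said, since the documents give neither utilities nor a cost-effectiveness threshold. It is worth acting on because the study treats cost-effectiveness as part of a key objective, the visit already exists, and the value is lost for each patient who passes day 30.

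**What to change.** - **7.2.1 and 8.2(4):** add the EQ-5D to the existing 30-day column, and collect it at reoperation visits to inform the utility of the reoperation state.
- **8.2(14):** use the 30-day value as the early postoperative utility in the Markov model. Report the ICER under at least two paths from day 30 to 1 year, one with early return to the 1-year level and one linear. Linear interpolation alone should not be relied on, because it can overstate a short-lived difference about sixfold (step 4).

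The cost is one short self-completed form and one EDC page per patient, a further form for those reoperated, and a protocol amendment. No scheduled visit is added. The remedy is partial: nothing would be measured between 30 days and 1 year, and the ±14-day window means the early value is taken between day 16 and day 44.
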